**Neutralizing antibody titers assay**

Anti-SARS-CoV-2 neutralizing antibodies will be measured in plasma samples using an HIV-1 backbone expressing firefly luciferase as a reporter gene and pseudotyped with the SARS-CoV-2 Spike glycoprotein^4,5^. Samples with a neutralizing activity of at least 50% at a 1:160 dilution will be considered positive and used to perform titration curves and ID50 calculations. Determination of the ID50 will be performed using a 4-parameter nonlinear regression curve fit measured as the percent of neutralization determined by the difference in average relative light units (RLU) between test wells and pseudotyped virus controls. In order to perform the ID50 calculations, the lack of fit test will have a p-value > 0.1. The top values will be constrained to 100 and the bottom values will be set to 0.

**Intervention and comparison**

The early plasma group will receive convalescent plasma on the day of enrolment. The deferred plasma group will receive convalescent plasma only if a prespecified worsening respiratory function criterion is met during hospitalization (Pa02/Fi02 <200) or, if the patient still requires hospitalization for symptomatic COVID-19 >7 days after enrolment.

The transfusion will consider a total of 400 mL of ABO compatible convalescent plasma, constituted by two 200 mL units separated by 24 hours. Plasma will be administered at a rate of 100 mL/h with close clinical monitoring. In both groups cointerventions including antibiotics, antivirals, heparin thromboprophylaxis, and immunomodulators such as steroids and tocilizumab will be allowed under the institutional protocol.

**Outcomes**

**Primary Outcomes:**

Composite outcome of mechanical ventilation and/or hospitalization longer than 14 days and/or in hospital-death

**Secondary Outcomes:**

- Clinical: days of oxygen requirement; days in mechanical ventilation; days of high-flow nasal cannula (HFNC) requirement; multiple organ dysfunction score (SOFA) (day 0, 3 and 7); days in intensive or intermediate care unit (ICU); time to respiratory failure development (Pa0_2_/FiO_2_<200 or, if arterial blood gases are not available on that day, a sustained Sa02/Fi02< 214 will be considered equivalent); length of hospitalization; 30 day-mortality.
- Microbiological: SARS-Cov2 PCR clearance in nasopharyngeal swab (days 0, 3 and 7)
- Inflammatory markers kinetics: lymphocyte count, C-reactive protein, procalcitonin, lactate dehydrogenase (LDH), D-dimer, ferritin and IL-6 evolution on days 0, 3, and 7.
- Radiologic: chest CT scan pneumonia score or portable chest X-ray progression between days 0 and 5.

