**Follow-up**

The follow-up for efficacy outcomes will conclude at hospital discharge. Safety outcomes will be reported until 30 days after hospital discharge.

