**Statistical Analysis Plan**

Continuous variables will be shown as mean and standard deviation for normally data or median and interquartile range elsewhere. Categorical variables will be shown as the number of cases and percentages

Primary outcome

We will assess the effect of early plasma compared to delayed plasma on the primary binary outcomes through chi-squared tests or Fisher’s exact test when appropriate, and odds ratios will be presented together with 95% CI and p-values. In addition, as an exploratory analysis we will adjust for age and SOFA score at enrolment, and clinically significant baseline variables if they result imbalanced between both study arms, as fixed (individual-level) effects, using logistic regression. Values of p<0.05 (2 tails) will be considered.

Secondary outcomes

We will assess the effect of early plasma compared to delayed plasma on the secondary binary variables through chi-squared tests or Fisher’s exact test when appropriate. For continuous variables with normal distribution we will use the t-test, and for continuous variables with non-normal distribution the Wilcoxon-rank-sum test or Mann-Whitney U test for comparisons. Additionally, we will analyze binary variables using logistic regression. Numerical variables will be examined using generalized linear models with log link function and gamma family function. Treatment effects, crude and adjusted, will be presented as exponentiated coefficients, i.e. odds ratios, hazard ratios or incidence rate ratios, respectively and treatment effect estimates will be presented with 95% CI.

To test difference between Kaplan-Meier estimates in survival analysis, we will use the Log-Rank test and/or Cox proportional hazard models for time-to event variables.

For the analysis of paired continuous variables, we will use Wilcoxon matched-pairs signed-rank test.

Statistical significance will be defined using a 2-sided significance level of α = .05.

Immune response subgroup analysis

A pre-planned analysis of baseline neutralizing antibodies titers and anti-SARS-CoV-2 IgG titers progression (on days 0, 3, 7), is planned for participants from the early plasma group and for the subset of participants from the deferred plasma group who will not have yet received plasma on those scheduled days. Groups will be compared through Chi-squared tests or Fisher’s exact test when appropriate.

Statistical significance will be defined using a 2-sided significance level of α = .05.

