**Handling of missing data and dropouts**

Patient with incomplete follow-up or protocol violations, regardless of the reason, will be included in the primary outcome analysis by intention-to-treat (ITT) principle.

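### The five duration outcomes have no rule for patients who die, so the arms are compared unfairly when mortality differs, in a direction set by when deaths occur

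*Combined protocol and SAP*

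**What the plan says.** Under Secondary Outcomes, the protocol lists "days of oxygen requirement; days in mechanical ventilation; days of high-flow nasal cannula (HFNC) requirement", days in an intensive or intermediate care unit, and then "length of hospitalization; 30 day-mortality". The five durations are plain counts of days. None is defined as days alive and free of the support. SOFA at days 0, 3 and 7 is in the same list.

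The Statistical Analysis Plan assigns a t-test to normally distributed continuous secondary variables and, "for continuous variables with non-normal distribution the Wilcoxon-rank-sum test or Mann-Whitney U test for comparisons". It adds: "Numerical variables will be examined using generalized linear models with log link function and gamma family function". It also says "we will use the Log-Rank test and/or Cox proportional hazard models for time-to event variables", but ties none of the five durations to that option and does not say whether death would be an event, a censoring or a competing event.

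The section on missing data and dropouts says only that patients with incomplete follow-up or protocol violations "will be included in the primary outcome analysis by intention-to-treat (ITT) principle". It does not mention death or the secondary outcomes. The Follow-up section states: "The follow-up for efficacy outcomes will conclude at hospital discharge".

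**The concern.** A duration of support or stay ends either because the patient recovers or because the patient dies. A raw count of days treats the two alike. A patient ventilated on day 2 who dies on day 5 contributes 3 ventilator days and ranks better than a survivor ventilated for 10 days.

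The plan is also at odds with itself here. A death in hospital on day 5 is a failure in the primary composite, yet the same patient contributes a short stay of 5 days to length of hospitalization.

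At stake are the estimates, confidence intervals and p-values of five clinical secondary outcomes. SOFA at days 3 and 7 has a related gap: a patient who has died has no value, and no rule says what replaces it. In an open-label trial, a scoring rule chosen after the deaths are known would be open to the charge that it was driven by the data.

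**Working it through.** **The plan's own figure.** The documents give no number for the duration outcomes. The only figure to reproduce is the sample size, used here for the arm size. With 54.8% v 20%, two-sided 5%, 80% power and pooled proportion (0.548 + 0.20)/2 = 0.374:

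n = [1.960·√(2·0.374·0.626) + 0.842·√(0.548·0.452 + 0.20·0.80)]² / 0.348² ≈ 29.1, so 30 per arm.

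The arcsine formula gives 29, as does 55% v 20%. Power at 29 per arm is 79.8%. The stated 29 per arm is therefore reproduced within rounding and choice of formula, and is used below.

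**Ventilator days by hand.** Assume 30% of each arm is ventilated. In arm B all survive with 10 ventilator days. In arm A half of those ventilated die after t days and the rest have 10 days.

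- Arm B: 0.30 × 10 = 3.0 days.
- Arm A: 0.15 × 10 + 0.15 × t = 1.5 + 0.15t.
- t = 3: 1.95 days, a ratio of 0.65, so the deadlier arm looks 35% better.
- t = 10: 3.0 days, no difference, although 15% of arm A has died.
- t = 12: 3.3 days, so the deadlier arm looks worse.

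The direction thus turns on whether deaths come before or after the usual duration in survivors.

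**Length of stay by hand.** Assume mortality of 10% v 25%, a mean stay of 12.5 days in survivors, and deaths at 7.5 days on average.

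- Mean stay: 0.90 × 12.5 + 0.10 × 7.5 = 12.0, against 0.75 × 12.5 + 0.25 × 7.5 = 11.25. The deadlier arm looks better.
- Hospital-free days to day 30, with death scored 0 and stays beyond 30 days ignored: 0.90 × 17.5 = 15.75, against 0.75 × 17.5 = 13.125. The order is now correct.

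**The planned rank test.** Means do not show what the rank test would do, so hospital stay was simulated: 29 per arm, 4,000 runs, Mann-Whitney test at two-sided 5%. All inputs other than the arm size and the test are assumptions. Survivors' stay has the same distribution in both arms (log-normal, median 10 days, log-SD 0.6, capped at 30). Arm A has the first mortality shown. The last column scores death as 31 days, worse than any survivor.

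| Deaths A v B | Days of death | Mean raw stay A v B | A shorter on average (runs) | Raw days: significant for A / for B | Death worst: significant for A / for B |
|---|---|---|---|---|---|
| 10% v 10% | 2–7 | 11.4 v 11.4 | 49% | 2.2% / 2.1% | 2.5% / 2.2% |
| 20% v 10% | 2–7 | 10.6 v 11.4 | 67% | 7.7% / 0.6% | 0.4% / 9.4% |
| 30% v 10% | 2–7 | 9.9 v 11.4 | 80% | 18.9% / 0.2% | 0.0% / 26.8% |
| 20% v 10% | 5–20 | 12.2 v 12.2 | 49% | 2.0% / 3.2% | 0.6% / 10.0% |
| 30% v 10% | 5–20 | 12.3 v 12.2 | 47% | 1.8% / 3.4% | 0.1% / 26.0% |

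With equal mortality the test behaves as it should. With early excess deaths it leans towards the deadlier arm. With later deaths that lean disappears, but raw days hardly register the excess mortality.

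**The case against.** - **These are secondary outcomes in a 58-patient phase II trial.** Death counts in the primary composite, and 30-day mortality is in the same list as the durations, so a reader would see excess deaths next to a shorter stay. This stands, and it is why the point is an improvement that should be made and not a threat to the main conclusion. It does not correct the five comparisons themselves.
- **The reversal rests on early deaths.** A reader might infer that whichever arm has fewer deaths will look worse on these outcomes. The documents do not support that. They give no timing of deaths, and the exclusion of patients with PaO2/FiO2 below 200, on ventilation or with a do-not-resuscitate indication makes deaths after long support quite possible. In the hand calculation, deaths at 12 days reverse the sign. This objection stands in full as to direction.
- **A significant false signal is uncommon.** Even with early deaths and mortality of 20% v 10%, it appears in 7.7% of runs. That is fair, though under a correct rule the figure is 0.4%.
- **Length of stay might be analysed by log-rank or Cox.** The plan allows those methods for time-to-event variables, so a raw comparison is inferred from the outcome names and the listed tests, not stated outright. But the only outcome in the list worded as a time to an event is respiratory failure, and the plan gives no treatment of death for the Cox option either.
- **Death may be rare.** A reader might take its place in the composite as a sign that it is frequent. The documents give no death rate, and a component may be included for its importance. With few deaths, or equal deaths in the two arms, the distortion is small.

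**Conclusion.** The omission is real: five durations are compared between arms with no rule for deaths. When mortality differs, the comparison is distorted. Early excess deaths can make the deadlier arm look better; late ones leave raw days largely blind to the harm. At an assumed 30% v 10% mortality, a significant result for hospital stay favours the deadlier arm in 18.9% of runs if deaths fall on days 2–7. If they fall on days 5–20, the safer arm is favoured in only 3.4% of runs, against 26.0% with death ranked worst. These sizes rest on assumed death rates, death times and stays; only the arm size and the test come from the plan. The direction in this trial cannot be predicted from the documents. The primary outcome and 30-day mortality are not affected.

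**What to change.** In Secondary Outcomes and the Statistical Analysis Plan:

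1. For the between-arm comparison, analyse days alive and free of each of oxygen, HFNC, ventilation, ICU and hospital to day 30 after randomisation. Score death by day 30 as the worst value, below a survivor with zero free days. Compare by rank-sum test with a Hodges-Lehmann shift and 95% CI.
2. State how days after discharge count, since efficacy follow-up ends there: as support-free if the patient is alive at day 30, except for any known readmission or home oxygen. Report this as an assumption.
3. Keep raw durations as description, with mortality shown beside them.
4. For SOFA at days 3 and 7, give patients who have died the worst rank.

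The cost is mainly wording. The data collection section already records respiratory support daily to day 30 or discharge, and all-cause mortality at 30 days. It does not list oxygen use or readmission after discharge, hence the stated convention. The drawbacks are that the outcome mixes death with duration and relies on the post-discharge assumption. Time to discharge with death as a competing event would be a reasonable alternative for length of stay. Whichever rule is chosen should be fixed before outcomes are examined by arm.

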**Subgroup analysis:**

- Immunological: IgG SARS-CoV2 titers progression (days 0, 3, 7) in participants receiving immediate plasma versus participants not receiving plasma.
- Neutralizing antibodies capacity on the day of enrolment.

**Safety Outcomes**

Adverse events (AE) will be defined as any unfavourable symptom, sign or test abnormality that is temporarily compatible with plasma transfusion. That includes COVID-19 symptoms that were not present at admission, complication associated to protocol issues (phlebitis, extravasation, etc.) and chronic disease worsening. Serious adverse event (SAE) will be defined as death, life-threatening adverse event, prolongation of hospitalization due to an adverse even, and any adverse event that requires an intervention. Death attributed to COVID-19 infection was not considered an SAE.

Any adverse event will be characterized by seriousness, duration, causality suspicion and intervention requirement. To establish causality the temporal relationship, previous pattern of transfusion-related AEs and exclusion of other causes will be reviewed.

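### Adverse events are tied to a transfusion that only some deferred patients receive, so AE and SAE counts are not ascertained alike in the two arms, although all-cause mortality remains comparable

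*Combined protocol and SAP*

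**What the plan says.** Safety appears in both the general and the specific objectives. Under Safety Outcomes, an adverse event is "any unfavourable symptom, sign or test abnormality that is temporarily compatible with plasma transfusion"; I read the adverb as meaning compatible in time. The next sentence widens the content but opens by referring back to that definition: "That includes COVID-19 symptoms that were not present at admission, complication associated to protocol issues (phlebitis, extravasation, etc.) and chronic disease worsening".

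On seriousness, the section first says "Serious adverse event (SAE) will be defined as death", followed by other criteria, and then "Death attributed to COVID-19 infection was not considered an SAE". On causality it says "To establish causality the temporal relationship, previous pattern of transfusion-related AEs and exclusion of other causes will be reviewed". It does not say who makes the judgement or whether that person knows the arm.

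Exposure differs by design. Under Intervention and comparison, the early group is transfused on the day of enrolment, whereas "The deferred plasma group will receive convalescent plasma only if a prespecified worsening respiratory function criterion is met during hospitalization", or if the patient still needs hospital care for symptomatic COVID-19 more than 7 days after enrolment.

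On duration, Follow-up states "Safety outcomes will be reported until 30 days after hospital discharge". The Statistical Analysis Plan describes no AE or SAE tabulation, safety population or at-risk period.

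**The concern.** An AE definition that depends on treatment works when both arms receive an infusion at the same time. Here one arm receives plasma at once, and the other receives it late, conditionally or never. The definition gives no reference time for a deferred patient who has not been, or never is, transfused. Yet the listed content (new COVID-19 symptoms, worsening of chronic disease) also occurs without plasma. Events with the same cause and frequency could be logged in one arm and not in the other.

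The exemption for COVID-19 deaths adds a second problem. Causality rests partly on excluding other causes, and every participant has COVID-19, so a competing explanation is always available. At stake is the safety objective: the AE and SAE tables, and the interim look at safety data that would use the same counts, could misstate non-fatal harm.

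**Working it through.** The plan attaches no figure to safety, so there is none to reproduce. The check sets the sections side by side and then bounds the distortion.

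**Side by side**

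| Question | Early arm | Deferred arm |
|---|---|---|
| Who is transfused | All, on the day of enrolment | Only those with PaO2/FiO2 below 200, or still hospitalised with symptoms more than 7 days after enrolment |
| Reference time for an AE | Enrolment | The later transfusion, or none |
| Selection of those who can have an AE | None | Worsening or prolonged stay |

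Restricting the comparison to transfused patients does not help, because the deferred recipients are selected for a poor course.

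The SAE rule is also inconsistent within itself. A new COVID-19 symptom can be an AE, and if life-threatening an SAE, but a COVID-19 course that ends in death is not one.

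**Inputs.** 29 patients per arm (Sample Size). The share f of deferred patients ever transfused and the true event rate b are not in the documents; both are assumptions.

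**Bound on the ratio.** Suppose plasma has no effect on events. Let b_T and b_U be the event rates in deferred patients who are and are not transfused, so that b = f·b_T + (1 − f)·b_U. Let g be the fraction of events in untransfused patients that staff log anyway.

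Recorded ratio, early to deferred = b / [f·b_T + g·(1 − f)·b_U].

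- If everything is logged (g = 1), the ratio is 1.
- If nothing is logged in untransfused patients (g = 0) and rates are equal (b_T = b), the ratio is 1/f, or 29/(29f) in patients able to have an AE.
- If transfused deferred patients are sicker (b_T above b), the ratio falls below 1/f.

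Results at the upper end: f = 0.40 gives 1/0.40 = 2.50; f = 0.55 gives 1/0.55 = 1.82; f = 0.70 gives 1/0.70 = 1.43. The value 0.55 is near the 54.8% control-arm rate assumed for the primary outcome. Many such patients would probably meet a trigger for deferred plasma, but the documents do not state f. The formula treats a transfused deferred patient's whole stay as countable. Events before a late transfusion would also be missed, which is why the bound is only approximate.

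**What this could do to a comparison.** With p1 = b, p2 = f·b, n = 29 and p̄ the mean of p1 and p2, the approximate chance of p < 0.05 is Φ{[(p1 − p2) − 1.96·√(2p̄(1 − p̄)/n)] / √[(p1(1 − p1) + p2(1 − p2))/n]}.

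| True rate b | f | Recorded early vs deferred | Spurious difference | Chance of p < 0.05 |
|---|---|---|---|---|
| 40% | 0.20 | 40% vs 8% | 32 points | 83% |
| 40% | 0.40 | 40% vs 16% | 24 points | 53% |
| 40% | 0.60 | 40% vs 24% | 16 points | 25% |
| 20% | 0.20 | 20% vs 4% | 16 points | 46.5% |
| 20% | 0.40 | 20% vs 8% | 12 points | 26% |
| 20% | 0.60 | 20% vs 12% | 8 points | 13% |

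These rows share the g = 0, equal-rate assumptions and are upper-end illustrations.

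**Window.** Safety follow-up ends 30 days after discharge, so its length is stay plus 30 days. If enrolment is on admission, an assumed 5-day stay gives 35 days and a 20-day stay gives 50. Length of stay is itself an outcome, so the window may differ between arms.

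**The case against.** The strongest reply is that the plan keeps other safety information that does not depend on transfusion. Data collection and management lists all-cause mortality at discharge and at 30 days, and cause of death. Thirty-day mortality is a secondary outcome, and in-hospital death of any cause is in the primary composite, analysed by intention to treat. Daily SOFA, haemodynamics and respiratory support, and troponin, pro-BNP and D-dimer on set days, are listed without restriction to transfused patients. This stands. A reader might infer that the arms cannot be compared for harm at all, or that no background data exist in untransfused patients. The documents do not support either reading; the gap is in the AE and SAE counts.

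Second, the safety objective is not worded as a comparison, and no between-arm AE test is planned. That is true, but a randomised trial with a safety objective will have its AE counts read by arm, and they need a common basis.

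Third, the AE wording is ambiguous. New COVID-19 symptoms are anchored to admission, and death is listed without a transfusion qualifier, so staff might log events in untransfused patients. This is why 1/f is an upper figure, but the text does not tell them to do so.

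Fourth, a reader might infer that unblinded investigators attribute deaths and that the SAE count therefore favours plasma. The documents name no assessor, and the exemption applies to both arms, so the direction of any error is unknown. What can be said is that the trial is open-label and that blinding is stated only for the analyst and for the radiologist who reads replacement X-rays.

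**Conclusion.** The concern holds for AE counts and the SAEs derived from them. As written, they are ascertained on a different basis in each arm and give no fair between-arm estimate of non-fatal harm. The size depends on the unknown f: at most about 1/f, for example 1.8-fold at an assumed f = 0.55, with equal event rates and no AE recorded in untransfused patients. It shrinks towards no distortion as more events in untransfused patients are logged.

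It also holds that a death to which plasma contributed can leave the SAE count through an attribution with no stated assessor or blinding. Such a death stays in the all-cause mortality comparison. I take the 30 days there as running from enrolment, since the plan does not give the starting point.

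**What to change.** - Define an AE as any untoward event from randomisation in every randomised patient, transfused or not, with suspected relation to transfusion as a separate field.
- Report every death in the safety tables by arm, with attributed cause as a separate field. State who attributes cause and, where feasible, keep that person blind to arm.
- Compare arms over one common window from randomisation, for example to day 30, and list later events separately. Add this tabulation to the Statistical Analysis Plan.
- Report reactions timed to a transfusion separately, among transfused patients.

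The cost is mainly protocol and case report form wording, plus more AE entries, most of them related to COVID-19. Daily records stop at discharge or day 30, so patients discharged early need AE contact to day 30. The existing safety follow-up already covers this: discharge on day d means follow-up to day d + 30, which is never before day 30.

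### The serious adverse event definition takes in every adverse event that needs an intervention, with no severity limit, so SAE totals by arm are hard to interpret and can be distorted in either direction

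*Combined protocol and SAP*

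**What the plan says.** Under Safety Outcomes, an AE is "any unfavourable symptom, sign or test abnormality that is temporarily compatible with plasma transfusion" (I read the adverb as meaning compatible in time). The text continues: "That includes COVID-19 symptoms that were not present at admission, complication associated to protocol issues (phlebitis, extravasation, etc.) and chronic disease worsening".

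An SAE is then reached by any of four routes: death, a life-threatening event, a hospital stay prolonged by an AE, or "any adverse event that requires an intervention". The fourth route carries no severity grade, type of treatment or threshold. The only disease-related exclusion is for fatal events: "Death attributed to COVID-19 infection was not considered an SAE".

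For recording, the section states: "Any adverse event will be characterized by seriousness, duration, causality suspicion and intervention requirement". Severity grade is not among these attributes. Causality is reviewed as follows: "To establish causality the temporal relationship, previous pattern of transfusion-related AEs and exclusion of other causes will be reviewed".

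Safety is one of the specific objectives (Objectives), and safety data are part of the interim review (Interim analysis). The Statistical Analysis Plan names no safety analysis and no comparison of SAEs between arms.

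**The concern.** The fourth route has no floor. Taken literally, a cannula re-sited for phlebitis, or a new symptom after transfusion that is given a drug, is an SAE in the same sense as a life-threatening reaction. Under Intervention and comparison, antibiotics, antivirals, heparin, steroids and tocilizumab are allowed in both arms, so treated events that are not severe are to be expected.

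At stake is the reading of the SAE count, which is the natural headline figure for the safety objective and for the interim review. If it mixes trivial with grave events in unknown proportion, a difference between arms cannot be read as harm, and the absence of a difference cannot be read as reassurance.

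**Working it through.** **1. What qualifies.** Setting the sentences of Safety Outcomes side by side:

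| Event | AE under the definition? | SAE under the definition? |
|---|---|---|
| Phlebitis, treated | Yes, named | Yes, by the intervention route |
| COVID-19 symptom absent at admission, compatible in time with transfusion, treated | Yes | Yes, by the intervention route |
| COVID-19 symptom already present at admission, unchanged | Not by the sentence on symptoms | No |
| Life-threatening transfusion reaction | Yes | Yes |
| Death attributed to COVID-19 | Excluded from SAEs | No |

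The definition gives rows 1, 2 and 4 the same classification.

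**2. Who can have an AE.** AEs must be compatible in time with a transfusion. The early arm is transfused on the day of enrolment. The deferred arm is transfused only on respiratory worsening or if still in hospital for symptomatic disease more than 7 days after enrolment (Intervention and comparison). A deferred patient who meets neither condition receives no plasma. Background treated events may therefore be similar in the two arms or more frequent in the early arm, depending on how sites apply the definition. The documents do not settle which.

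**3. Inputs for an illustration.** The safety section has no figure to reproduce. The one design figure used is 29 per group (Sample Size). The usual two-sided formula at 5% and 80% power, without continuity correction, gives 30 per group for 54.8% against 20%, and 29 for a difference of exactly 35 points, so the stated figure is sound for this purpose. Everything else is **assumed**: the rate *s* of truly serious events, and the rate *b* of patients with an event that is an SAE only through the intervention route, independent of *s*. Then

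P(SAE) = 1 − (1 − s)(1 − b),

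and the arms are compared by Fisher's exact test, two-sided 5%, with exact power. The plan does not schedule this test. It serves only as a yardstick.

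**4. Equal background, true difference (s = 25% early, 3% deferred).** For b = 20%: early 1 − 0.75 × 0.80 = 40.0%; deferred 1 − 0.97 × 0.80 = 22.4%.

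| b, both arms | Early | Deferred | Chance of p < 0.05 |
|---|---|---|---|
| 0% | 25.0% | 3.0% | 53% |
| 20% | 40.0% | 22.4% | 21% |
| 40% | 55.0% | 41.8% | 11% |
| 60% | 70.0% | 61.2% | 6% |

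With s = 20% against 2%, the chance is 38% with no background and 22%, 10% and 6% at b = 10%, 30% and 50%; the risk ratio falls from 10 to 2.4, 1.4 and 1.2. With s = 10% against 2%, it is about 4% with no background and stays at 3% to 5% for b of 20% to 60%.

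**5. Unequal background, no true difference (s = 3% in both arms).** The deferred background is assumed to be half the early one. For 20%/10%: early 1 − 0.97 × 0.80 = 22.4%; deferred 1 − 0.97 × 0.90 = 12.7%.

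| b early / deferred | Early | Deferred | Chance of p < 0.05 |
|---|---|---|---|
| 20% / 10% | 22.4% | 12.7% | 8% |
| 40% / 20% | 41.8% | 22.4% | 25% |
| 60% / 30% | 61.2% | 32.1% | 50% |

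**6. Unequal background, true difference (25% against 3%).** With the same three pairs of backgrounds the chance is 56%, 63% and 76%, against 53% with none. Here the definition exaggerates a real difference instead of diluting it.

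**The case against.** The strongest reply is that the plan already collects what is needed to sort the events. Causality and intervention requirement are recorded for every AE, and causality is reviewed against timing, known transfusion reactions and other causes. A serious plasma reaction can therefore be told apart from a treated phlebitis in the listings. This stands in part: the separation is possible, but nothing in the plan requires it, and sorting events after the fact in an open-label trial is open to challenge.

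A second reply is that a broad criterion errs towards over-reporting, a defensible caution in a single-center Phase II trial of 58 patients, and that narrowing it brings in investigator judgement where treatment is known. The cost of judgement is real and is taken up under the fix.

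A third is that 29 per arm gives little power for uncommon serious reactions under any definition, and that no test of SAEs is planned. Both statements are correct. They limit the weight of the power figures but do not make the count easier to interpret.

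A reader might infer three stronger claims, which the documents do not support:

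- **That the rule hides a transfusion signal.** This holds only if background is similar in both arms. Steps 5 and 6 show the opposite error under unequal background.
- **That recording seriousness and intervention requirement separately contradicts the definition.** Intervention is one of four routes to seriousness. An event can be serious by prolonged stay without an intervention, so recording both is overlap, not contradiction.
- **That nearly every AE becomes an SAE.** The documents give no rates, and a COVID-19 symptom counts only if it is absent at admission and compatible in time with transfusion.

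**Conclusion.** The point holds as a weakness of definition. The intervention route has no severity limit, so the SAE total mixes minor treated events with life-threatening ones, and its comparison between arms can be diluted or inflated. The direction depends on how background treated events divide between the arms, and the documents leave that open.

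The size cannot be established, because no AE or SAE rates are given. The illustration covers assumed backgrounds of 10% to 60% and assumed true rates of 2% to 25%. It shows that either error can be large, and also that for rarer reactions (10% against 2%) the definition hardly changes an already very low power. No planned test is invalidated and the primary analysis is untouched. This is a cheap improvement to the safety reporting.

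**What to change.** In Safety Outcomes, limit the fourth route to AEs that need intervention to prevent one of the other listed SAE outcomes (death, a life-threatening event, a prolonged stay). Keep intervention requirement as the separate descriptor already recorded for each AE. State in the Statistical Analysis Plan that SAEs will be tabulated by arm, qualifying criterion and causality at the interim and final reports.

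The cost is one sentence in the protocol, matching case report form guidance and one table specification, with no new patient data. The downside is that the narrower criterion needs an investigator judgement in an open-label trial. Listing all treated AEs by arm beside the SAE table limits this, since a shift of events between categories would then be visible.

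The change does not remove the difference in exposure between arms. As long as AEs are tied to transfusion, the tables should also show how many patients in each arm received plasma.
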